# “Body & Brain”: effects of a multicomponent exercise intervention on physical and cognitive function of adults with dementia - study protocol for a quasi-experimental controlled trial

**DOI:** 10.1186/s12877-021-02104-1

**Published:** 2021-03-04

**Keywords:** Neurocognitive disorder, Multimodal, Functionality, Cognition

## Abstract

**Background:**

Dementia is a leading cause of death and disability that was declared as one of the greatest health and social care challenges of the twenty-first century. Regular physical activity and exercise have been proposed as a non-pharmacological strategy in disease prevention and management. Multicomponent Training (MT) combines aerobic, strength, balance and postural exercises and might be an effective training to improve both functional capacity and cognitive function in individuals with dementia (IwD). Nevertheless, data on the effects of MT in IwD are still limited and the extent to which IwD can retain improvements after an exercise intervention still needs to be elucidated. The aim of “Body & Brain” study is to investigate the effects of a 6-month MT intervention and 3-month detraining on the physical and cognitive function of IwD. Additionally, we aim to explore the impact of this intervention on psychosocial factors and physiologic markers related to dementia.

**Methods:**

This study is a quasi-experimental controlled trial using a parallel-group design. The study sample consists of community-dwelling individuals aged ≥60 years who are clinically diagnosed with dementia or major neurocognitive disorder. Participants will be either allocated into the intervention group or the control group. The intervention group will participate in MT biweekly exercise sessions, whereas the control group will receive monthly sessions regarding physical activity and health-related topics for 6 months. The main outcomes will be physical function as measured by the Short Physical Performance Battery (SPPB) and cognitive function evaluated using the Alzheimer Disease Assessment Scale – Cognitive (ADAS-Cog) at baseline, after 6-months and 3-months after the end of intervention. Secondary outcomes will be body composition, physical fitness, daily functionality, quality of life, neuropsychiatric symptoms and caregiver’s burden. Cardiovascular, inflammatory and neurotrophic blood-based biomarkers, and arterial stiffness will also be evaluated in subsamples.

**Discussion:**

If our hypothesis is correct, this project will provide evidence regarding the efficacy of MT training in improving physical and cognitive function and give insights about its impact on novel molecular biomarkers related to dementia. This project may also contribute to provide guidelines on exercise prescription for IwD.

**Trial registration:**

ClinicalTrials.gov – identifier number NCT04095962; retrospectively registered on 19 September 2019.

## Background

Dementia is considered one of the main age-related health problems impacting the modern society [1, 2]. Also designated as major neurocognitive disorder, these umbrella terms are used to describe a set of diseases that are mostly chronic or progressive, affecting the brain and several cognitive functions [3, 4]. By 2050, it is expected that 132 million people will suffer from dementia worldwide [1]. Therefore, the World Health Organization (WHO) has already recognized this condition as a global health priority [5] and alerted countries for the need to develop and implement national intervention plans to prevent, treat and care for dementia [6]. In Portugal, the prevalence rate for dementia in 2017 was 9.23% in community-dwelling older adults [7].

Age is the primary non-modifiable risk factor for dementia [8]. Livingston et al. (2020) described 12 potentially modifiable risk factors that, when addressed might prevent or delay up to 40% of dementia cases [2]. Of those, addressing physical inactivity (e.g., by increasing the levels of physical activity), particularly in later life, may be a potential strategy to prevent, or even delay the progression of cognitive impairment due to its effect on underlying physiologic mechanisms: the indirect effects on general cardiovascular health/fitness and neurological direct effects [9–11].

Individuals diagnosed with dementia (IwD) not only exhibit a significant decline in one or more cognitive domains that interfere with the person’s ability to perform activities of daily living (ADL), but also tend to reveal increased declines on physical fitness, as impaired aerobic capacity, muscle strength, agility, gait and balance [12–14]. Skinner, Ellis & Pa (2018) stated that exercise may positively impact IwD’s cognition, quality of life, functional status, sleep, mood and physical function [11], being these positive outcomes related to several cellular and molecular alterations [15]. Additionally, evidences suggest that exercise can counteract dementia-related pathogenic changes by preserving neuroplasticity trough neurogenesis, synaptogenesis and angiogenesis [15]. Hence, increasing data advocate regular moderate-intensity exercise as an effective strategy to improve general health status, reducing vascular risk factors, obesity, levels of inflammatory markers, improving metabolism and brain health in older adults with dementia [16]. However, results regarding exercise effects on cognitive function are still heterogeneous [17–19].

Although exercise interventions for IwD seem to be feasible and well tolerated, resulting in positive effects on ADL functionality for people at mild-to-moderate stages [17, 18], the therapeutic role of physical activity, particularly exercise, after dementia diagnosis still needs further evidence [20–22], − especially when considering community-based contexts and caregivers as participants on exercise sessions [23]. It also matters to highlight that the dose-dependent relationship remains unclear [11, 18, 24]. Therefore, research is needed to identify the triad: stage/type of dementia, FITT variables (frequency, intensity, type and time) of exercise intervention, and target outcome [11, 25].

Regarding exercise modality, Multicomponent Training (MT) [26] – combining aerobics, strength and balance exercises – seems to be effective at improving functional and cognitive performances in older adults with neurodegenerative disorders, particularly dementia [27–29]. Exercise programs previously developed by our group confirmed that a 6-month MT intervention can positively impact the physical and cognitive function of institutionalized older adults with Alzheimer's Disease (AD) [30, 31] and can be beneficial in physical fitness and ADL functionality performance among community-dwelling patients [25, 32]. However, the extent to which IwD can retain these improvements after the cessation of MT intervention still need to be elucidated [33] in order to understand how detraining affects functionality and cognition following the cessation of MT stimulus.

In addition to the most common analysis on cognition, physical fitness, daily functionality, neuropsychiatric symptoms, quality of life and caregivers’ burden [18, 34–36], several other parameters need to be further explored when considering the benefits of MT. These include the effect of exercise on body composition, cardiorespiratory fitness, vascular, inflammatory and neurotrophic blood-based biomarkers, and arterial stiffness.

The primary purpose of this study is to investigate the effects of a 6-month MT exercise intervention and 3-months of detraining on physical and cognitive function of older adults diagnosed with dementia. Secondarily, we aim to explore potential positive effect of MT exercise on IwD psychosocial and physiological outcomes. We hypothesize that exercise positively modulates body composition (e.g., by increasing lean mass and decreasing adiposity) and therefore may improve physical fitness and function. Additionally, it is described that exercise enhances cerebrovascular plasticity, peripheral biomarkers associated with brain blood flow and (neuro)inflammation, consequently attenuating cognitive decline or even improving cognitive function. The concomitant enhancements of physical and cognitive function in individuals with dementia may help to preserve or improve their functionality in ADL and manage behavioral and psychological symptoms of dementia (BPSD), reducing the caregiver’s burden and leading to improvements in quality of life.

## Methods and analysis

The “Body & Brain” study is registered with the US National Institutes of Health clinical trials registry (ClinicalTrials.gov – identifier number NCT04095962). This protocol report complies with the Standard Protocol Items: Recommendations for Interventional Trials (SPIRIT) 2013 checklist: recommended items to address in a clinical trial protocol and related documents [37].

### Trial design

This study is a multicenter quasi-experimental controlled trial with a parallel design, that will be conducted in a wide-ranging public and private settings (e.g., daycare centers and local community centers) in the Porto metropolitan area, Portugal. Participants will be recruited from community programs, daycare centers, psychiatric hospitals and clinics (i.e., outpatients followed within psychiatry or neurology specialists), Alzheimer’s and caregivers’ associations, municipalities, local journals, and social media. Advertisements will be made via phone calls, emails, informative flyers and presential and online meetings. In order to motivate and clarify concerns about the exercise sessions, a short MT session will be provided to exemplify and illustrate a typical session for individuals with dementia.

Eligible participants and caregivers will receive a complete explanation of the study purposes, risks and procedures. Following the best ethical procedures, informed consent will be obtained from interested dementia participants and from their main caregivers/legal representatives/significant person. After agreeing to participate and according to personal availability, participants will be allocated into a 6-month MT intervention (IG) or into a social activity group (CG) (see Fig. 1). All CG participants will be offered the possibility to participate in an exercise program after the end of the study cycle.

**Fig. 1 Fig1:**
[figure not shown]
Study Flow Diagram

Participants will be assessed at baseline, after 6-month of intervention, and 3-month follow-up after the end of intervention (Table 1). At baseline, sociodemographic (e.g., age and years of formal education), general clinical data (e.g., presence of comorbidities, pharmacological treatment, and falls) will be collected through a structured questionnaire, and dementia rating severity evaluation will be performed trough the Clinical Dementia Rating (CDR) outcome measurement [38]. During baseline assessments, participants will not be informed regarding to which group they belong. Data collection will be performed by well-trained and experienced researchers.

**Table 1 Tab1:** Description of methods and/or instruments to evaluate IwD and/or their caregivers/significant person/proxy decision-maker

	Domain	Measure	Data from	
			IwD	Caregiver
**Screening**	Informed Consent		X	X
	Anamnesis (sociodemographic and general clinical data)			X
	Clinical Dementia Rating		X	X
**Primary**^**a**^	Cognition			
	Cognitive Function	ADAS-Cog	X	
	Physical Fitness			
	Lower Limb Function	SPBB	X	
**Secondary**^**a**^	Cognition			
	Cognitive Function	MMSE	X	
		TMT		
	Physical Fitness			
	Cardiorespiratory Capacity	Modified Bruce Treadmill Test	X	
	Physical Fitness	SFT	X	
	Static Balance	One Leg Balance Test	X	
	Handgrip Strength	Handgrip Dynamometer	X	
	Body Composition and Anthropometry			
	Body Mass	DXA (Hologic QDR 4500, Explorer model, version 12.4)	X	
	Total Fat-free Mass			
	Fat Mass			
	Appendicular Skeletal Mass Index			
	Weight	Weighting Scale	X	
	Height	Stadiometer	X	
	Waist and Hip Circumferences	Measuring Tape	X	
	Quality of Life and ADL’s Functionality			
	Basic and instrumental ADL	Lawton & Brody IADL Scale		X
		Barthel Index		
	Quality of Life	QoL-AD	X	X
	Behavioral and Psychological Symptoms of Dementia			
	Neuropsychiatric Symptoms and Caregiver Distress	NPI		X
	Caregiver Burden			
	Caregiver Well-being and Subjective Burden	CarerQol-7D		X
		CarerQol-Vas		
	Blood-based Biomarkers and Hemodynamics			
	Systolic and Diastolic Blood Pressure	Digital Sphygmomanometer	X	
	Arterial Stiffness	Pulse Wave Velocity (SphygmoCor, AtCor Medical, Australia)	X	
	TG	Concentration in blood plasma	X	
	TC			
	LDL-C			
	HDL-C			
	HbA1c	HPLC		
	BDNF	ELISA	X	
	VEGF			
	CRP			
	sICAM-1			
	sVCAM-1			
	MMP-9			
	IL-6, IL-8, IL-10			
	TNF-alfa	CLIA	X	
	IGF-1			
**Confounders**^**a**^	Daily Physical Activity			
	Physical Activity Levels	Accelerometer-based activity monitors *GT9X+ Link* (ActiGraph)	X	

^a^*T0* Baseline, *T1* After 6-month intervention, *T2* 3-month follow-up

The same evaluator will be responsible to perform the same procedures along the three assessment periods, which will be subdivided in five separate moments (Table 2). The exercise professional who is going to provide the MT sessions will not be involved in any data collection.

**Table 2 Tab2:** Schedule for the different primary and secondary and outcomes, screening, and confounder evaluations of each assessment moment per evaluator

*Assessment moments per evaluator*	Prior to Assessment (only at baseline)	1st Cognition & Functionality^**a**^	2nd Cognition, QoL & Physical Fitness^**a**^	3rd Physical Activity Level^**a**^	4th ADL, QoL, BPSD & Caregiver Burden^**a**^	5th Body Composition, Cardiorespiratory Fitness, Hemodynamics & Blood-based Biomarkers^**a**^
***Evaluator 1***	CDR	MMSE TMT	ADAS-Cog QoL-AD patient		QoL-AD caregiver Carer-QoL NPI Barthel Index Lawton & Brody IADL Scale	
***Evaluator 2***		SPPB Handgrip strength	SFT One Leg Balance Test	7-day accelerometer-based monitor		
***Evaluator 3***	Informed Consent and anamnesis (sociodemographic and general clinical data)					VO2 Peak Consumption Anthropometry DXA Body Composition Blood Pressure Arterial Stiffness
***Laboratory***						Blood Analysis

^a^*T0* Baseline, *T1* After 6-month intervention, *T2* 3-month follow-up

### Participants

#### Eligibility criteria

This study will include individuals aged ≥60 years capable of walking autonomously without an assistive device or human assistance, and diagnosed with dementia or major neurocognitive disorder using accepted diagnostic criteria such as that established by the Diagnostic and Statistical Manual of Mental Disorders (DSM-IV-TR or DSM-5) [3], ICD-10 [39], or the NINCDS-ADRDA [40]. Potential participants must have been diagnosed by a physician for at least for 6-months. Participants diagnosed with Parkinson’s disease, Frontotemporal disease, Lewy bodies’ disease, Huntington’s disease or other rare forms of dementia can be included in the study as long as they do not exhibit significant motor/functional limitations. The exclusion criteria comprise disorders or conditions in which exercise is contraindicated such as unstable or ongoing cardiovascular and/or respiratory disorder; hospitalized individuals and/or recovering from surgery or rehabilitation; and presenting an advanced stage of dementia (e.g., scored 3-points in CDR or ≤ 10 points on MMSE) that could affect physical performance in the exercise training sessions or testing procedures.

#### Sample size

Sample size was estimated based on ANCOVA for the analysis of the differences [41]. To detect an adjusted 1 point (SD = 2.1) difference in SPPB after intervention between IG and CG with 80% power and an alpha level of 0.05, a total of 110 participants (55 participants per group) will be needed, already accounting for an estimated dropout of 25%. Sample size calculation was performed using G*Power 3.1.3 (Universität Düsseldorf, Düsseldorf, Germany) [42].

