### Statistical analysis plan

Descriptive statistics will be expressed as mean and standard deviation (SD) or as median and interquartile range (IQR) for continuous variables. Categorical variables will be expressed as frequency and percentages. Normal distribution will be analyzed by the Kolmogorov-Smirnov test with Lilliefors’ (K–S) significance correction and normal probability plots. Statistical comparisons at baseline characteristics will be performed using t-test or Mann–Whitney U-test for continuous variables and Chi-squared test or Fisher’s test for categorical variables.

Age, gender, level of education, dementia type/stage, and other variables will be considered as potential confounders and adjustments will be performed in accordance to detect differences between experimental and control group.

The primary effect parameter will be the difference in the SPPB and ADAS-Cog tests between the experimental and control groups, considering the two different moments of evaluation (baseline and after 6-month of intervention). An analysis of variance (ANOVA) test with repeated measures adjusted for potential confounders will be performed for the intervention-related effects. When a significant F value is obtained, Bonferroni post hoc procedures will be used to evaluate pairwise differences. Additionally, mixed effects models will be performed in order to identify potential predictive factor associated with the changes in primary and secondary outcomes from baseline, post-intervention and over the 3-months detraining period.

A multivariable regression analysis will be performed in order to explore the association between cardiovascular and blood-markers, and cognition.

Statistical analyses will be conducted with the SPSS IBM Statistical Software version 25.0 (SPSS, Inc., Chicago, IL) for Windows with a significance level of *p* < 0.05.

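### The 110 participants stated for 80% power on SPPB do not follow from the printed inputs; they need either a smaller SD or a baseline correlation that the protocol does not give

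*Protocol article*

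**What the plan says.** The Sample size section of the protocol article names the method: "Sample size was estimated based on ANCOVA for the analysis of the differences". The target is given as "To detect an adjusted 1 point (SD = 2.1) difference in SPPB after intervention between IG and CG", followed by the result: "with 80% power and an alpha level of 0.05, a total of 110 participants (55 participants per group) will be needed". This number is "already accounting for an estimated dropout of 25" per cent. The section does not say whether the test is one- or two-sided, whether 2.1 is a raw or a covariate-adjusted SD, or what baseline correlation (or R²) was used.

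The Statistical analysis plan section describes a different primary test: "An analysis of variance (ANOVA) test with repeated measures adjusted for potential confounders will be performed for the intervention-related effects". It compares the groups over baseline and 6 months. The named covariates are age, gender, education and dementia type or stage, plus unspecified others.

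Two other places bear on this. The Primary outcome section treats a 1-point SPPB change as meaningful. The Trial status section says that recruitment ends once the expected number is reached.

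**The concern.** A 1-point difference with SD 2.1 is a standardised difference of 0.476. For 80% power at two-sided 5%, that calls for about 70 evaluable participants per group. The plan enrols only 55 per group and expects to lose a quarter of them.

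SPPB is the only outcome for which a sample size is given, and the figure of 110 decides when recruitment stops. If the power is really nearer 57% than 80%, the trial could easily miss the 1-point difference that it calls meaningful, and a null result would be read against a power claim that the printed figures do not support.

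**Working it through.** **Inputs from the Sample size section.** Difference 1 point; SD 2.1; power 80%; alpha 0.05; 55 per group; dropout 25%. Two-sidedness is my assumption. It fits the ANCOVA basis and the F test in the analysis section, because a two-group F test has no direction.

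**Evaluable number.** 110 × 0.75 = 82.5, or about 41 per group.

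**Attempt to reproduce 110 from the printed inputs alone (2.1 is the SD that the test uses)**

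- d = 1/2.1 = 0.476; for the F test, f = d/2 = 0.238.
- Normal formula: n per group = 2 × (1.960 + 0.842)² × 2.1² / 1² = 69.2, so 70 per group and 140 in total.
- Noncentral t: 71 per group, 142 in total. ANCOVA F test with one covariate: 141 in total.
- Dividing by 0.75: 140 gives 187, 141 gives 188, and 142 gives 189.3 (190 as two equal groups).
- Power at 41 per group: 57% (t or F); 58% by the normal formula. Power at 55 per group with no dropout: 70%.
- Difference detectable with 80% power at 41 per group: 2.802 × 2.1 × √(2/41) = 1.30 points (1.32 by noncentral t).

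The figure of 110 is not reproduced.

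**Attempt with 2.1 as the raw SD and ANCOVA on baseline**

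The residual SD is 2.1 × √(1 − ρ²), where ρ is the baseline-to-6-month correlation. At ρ = 0.64:

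- n per group = 69.2 × (1 − 0.64²) = 40.9, so 41.
- 41/0.75 = 54.7, so 55 per group and 110 in total.

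This reproduces the stated figure, with dropout applied correctly. Power at 41 per group over assumed correlations (noncentral t, one covariate):

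| Assumed ρ | Residual SD | Power |
|---|---|---|
| 0.50 | 1.82 | 69% |
| 0.60 | 1.68 | 76% |
| 0.65 | 1.60 | 80% |
| 0.70 | 1.50 | 85% |

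**The analysis actually planned**

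With two time points, the group-by-time test in a repeated-measures ANOVA compares mean change. If 2.1 is the raw SD at each visit, the SD of change is 2.1 × √(2(1 − ρ)). At 41 per group:

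| Assumed ρ | SD of change | Power |
|---|---|---|
| 0.64 | 1.78 | 71% |
| 0.65 | 1.76 | 72% |
| 0.71 | 1.60 | 80% |

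These figures include no variance reduction from the other covariates.

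**The case against.** The strongest reply is that the section says it used ANCOVA. Under ANCOVA with a raw SD of 2.1 and ρ of about 0.64, 110 comes out at two-sided 5%, with 80% power and correct dropout inflation. The word adjusted qualifies the difference and does not clearly qualify the SD. A journal article may also leave the correlation to a fuller document. Much of this stands. It rules out a flat statement that the trial needs 190 participants and has 57% power, because both figures depend on 2.1 being the SD that the test uses.

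Two further readings are tempting:

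- **A one-sided test with dropout forgotten.** The one-sided normal formula gives 54.5, so 55 per group before dropout. But the section says dropout is included, and nothing in it mentions a one-sided test.
- **Dropout added by multiplying by 1.25.** At ρ = 0.6, 69.2 × 0.64 = 44.3, and 44.3 × 1.25 = 55.4. That rounds up to 56, and so fits worse than the error-free route above.

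The documents show neither mistake.

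It is also fair to say that 71 to 72% for the change comparison leaves out any gain from confounder adjustment. That gain cannot be quantified from the document.

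The reply does not remove the point. The figure of 110 is recovered only by solving backwards for a correlation that the document does not give, and the recovery works for ANCOVA on baseline, not for the repeated-measures comparison that the article names as primary. Allocation follows personal availability, so any association between group and covariates would widen the adjusted estimate's variance. The ANCOVA gain above is therefore a best case.

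**Conclusion.** The concern holds in a conditional form. The printed inputs do not yield 110 with 25% dropout included. Under the two-sided assumption, what 110 delivers depends on the missing inputs:

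- **2.1 is the residual SD:** about 57% power, with about 188 to 190 enrolled needed for 80%.
- **2.1 is the raw SD, ANCOVA on baseline:** 69% to 85% over correlations of 0.5 to 0.7, with 80% reached at about 0.64 to 0.65.
- **2.1 is the raw SD, planned comparison of change:** 71 to 72% at that same correlation, and about 0.71 needed for 80%, before any other covariate gain.

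The correlations are assumptions; the document gives none. A reader might infer that the power claim is simply false. The document does not establish that. It establishes that the claim cannot be derived from what is printed, and that the one route that recovers it does not carry over to the stated primary analysis.

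**What to change.** Keep 110 and rewrite the Sample size paragraph so that it:

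- says whether 2.1 is a raw or a residual SD;
- gives the baseline-to-6-month correlation used and its source;
- states the sidedness;
- shows dropout applied as n/(1 − 0.25);
- bases the calculation on the same analysis that is named as primary;
- reports the power and detectable difference that about 82 evaluable participants give under those inputs, as a range if the correlation is uncertain.

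Do not print 57% or 1.3 points unless 2.1 is confirmed as the residual SD.

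The cost is one paragraph and no extra enrolment. The stated power may become less favourable.
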